**Types of interventions**

**Video-based intervention:** This intervention will provide a message to motivate participants to get tested for HIV. This message will be customized for three audiences based on self-identification: gay, non-gay men and trans. The videos will be framed within the health-belief model, which focuses on the attitudes and beliefs of individuals, and within the stages of change theory, which shows that people tend to progress through different stages on their way to successful behavioral change [46,47]. The videos will incorporate ways to overcome different reasons why MSM don’t get tested for HIV, the script of the videos will be refined during focus groups with the target population.

**Text-based intervention:** This intervention will provide a standard public health text message with an invitation to a free HIV/syphilis testing, the message will be similar in content to Web pages currently available at Latin American websites.

**Phase III: Evaluation of Outcome measures:**

In this phase we will compare the intentions to get tested and the proportion of participants tested for HIV from each of the study arms. The email addresses that participants self-reported on the online survey will be matched with those self-reported at the study site to allow us the identification of the experimental condition to which participants were randomized. For the analysis, the results of the surveys will be exported from the survey database into SPSS 13.0 software. We will use Mantel Hanzel to calculate the Relative Risk of intentions to get tested for HIV and Cox proportional hazards regression to calculate the Hazard Ratios of getting tested at our clinic among the study arms of the intervention. We will follow the intention to treat principle.

Consent form and Screening questionnaire

Exclusion

Do not meet inclusion criteria

Do not want to participate

Randomization

Allocated and received video-based intervention

Allocated and received text-based intervention

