The data collected by the survey will be stored in a relational database hosted on a secure server. Only the survey administrator will have access to the risk assessment data by logging in using an account name and password over a secure connection. Respondents will not be able to access their own or anyone else’s results. In the questionnaires, participants will not be asked for any personally identifiable information. However, they will be asked to provide their email address. This email address will be stored in the database and will allow us to identify the experimental condition to which participants who come to our site to be tested have been randomized..

**Eligibility Criteria:** In order to be randomized to one of the interventions the participants have to fulfill all of the following eligibility criteria: (1) be 18 years of age or older, (2) be a man and report having had sex with men, (3) be a resident of Lima, Peru, (4) answer the survey from Lima, Peru (5) not have been tested for HIV during the last year, (5) have an email address that when typed twice matched and, (6) do not report being HIV positive. All of these criteria will be evaluated during the risk assessment

**Randomization:** After the participant finishes the baseline risk assessmentand enters his email address, our system will immediately assess the validity of this email and the fulfillment of all the eligibility criteria. Only if both requirements are met will the computer randomly assign the participant to one of the two arms of the intervention (Figure 1). The randomization will be automatically done by an algorithm that evaluates each case and uses a random number generator to make an independent assignment. The resulting assignments should be roughly fifty percent to the intervention group and fifty percent to the control group.

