**Figure 1: Randomization Process**

**Sample size determination**

Our hypothesis is that a video-based intervention compared to a text-based intervention will increase the proportion of HIV testing by 12%. Assuming a proportion of HIV testing of 3.0% in our control intervention and 15.0% in our active intervention, our estimated sample size is 87 participants for each arm of the intervention. This will provide a good power (0.80, at alpha 0.05) to see an absolute difference of 12% in testing proportions between the two arms.

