## F. Protection of Human Subjects

Our grant proposal will be sent for review to the Institutional Review Board of the University of Washington in Seattle and the NGO Vía Libre in Lima, Peru.

Human Subjects Involvement and Characteristics: We will recruit through Internet MSM 18 years and older who voluntarily are willing to participate in our study and meet the following eligibility criteria: (1) be 18 years of age or older, (2) be a man and report having had sex with men, (3) be a resident of Lima, Peru, (4) answer the survey from Lima, Peru (5) not have been tested for HIV during the last year, (5) have an email address that when typed twice matched and, (6) do not report being HIV positive.

Collection of information:On the Internet, data will be collected via a secure website. The data from the survey will be kept confidential. Only authorized personnel will access the data by logging in using an account name and password. Data that have been exported into statistical software will be stored on an access-controlled computer in a locked room at Via Libre.

Respondents will not be able to access their own or anyone else’s survey. At the homepage of our study, we will tell the participants that they may skip any question they choose not to answer and that the testing for HIV is voluntary and they may decide not to come.

During the survey, respondents will be asked to enter their email address for storage in the database. This email will be later used in the clinic to identify to which arm of the intervention a participant belongs. This will be possible only if the participant discloses his email address through a written informed consent in our site.

Potential Risks: Potential risks of answering the questionnaire include feelings of discomfort or other psychological distress arising from the personal nature of some questions, and the internal conflicts that some men may experience between their values, attitudes, beliefs and behaviors. Potential risks of being tested for HIV include stress, anxiety and depression. If the HIV results are negative it can increase the percentage of unsafe sex which would increase the risk of becoming infected with HIV or other STI. If the tests are positive and get into the wrong hands, the participants may lose their job.

The needle used to draw blood for the tests may cause pain and participants may get a bruise after the procedure.

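### Self-reported email is the only link between arm and HIV test, with no fallback key, so a tester who cannot be matched is analysed without an event

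*Protocol*

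**What the plan says.** The section on evaluation of outcome measures (Phase III) makes the link by email: "The email addresses that participants self-reported on the online survey will be matched with those self-reported at the study site". It then commits the analysis to intention to treat, with a hazard ratio from Cox regression for testing at the study clinic.

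Section F (Protection of Human Subjects, collection of information) sets the condition for the link: "This will be possible only if the participant discloses his email address through a written informed consent in our site". The recruitment and consent text of Section F describes the clinic step. The coordinator explains how the survey data will be tied to the arm, the man signs consent to the test and to disclosing his email, and the counsellor records it. The same text says that no name, address, telephone number, identity number or other identifier will be requested. The study website description in the Methods promises no cookies.

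Two safeguards act at baseline. One eligibility criterion is to "have an email address that when typed twice matched". The Randomization paragraph adds an immediate automatic check that the email is valid, made before assignment. Its method is not described.

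The sample size text reads "Assuming a proportion of HIV testing of 3.0% in our control intervention and 15.0% in our active intervention", and concludes that "our estimated sample size is 87 participants for each arm of the intervention". It contains no allowance for failed linkage. The Limitations mention tests at other clinics and self-misrepresentation, but not failed linkage.

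**The concern.** The outcome is observed only if two entries of one self-reported item agree, the first made online and the second in person at a later time that the Protocol does not fix. The baseline checks address typing errors and possibly malformed addresses. As described, they do not show that the man will remember that address or give the same one at the clinic. If he does not, the clinic holds a real test with no arm, and his randomised record shows no test.

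The Protocol does not say that such a man is coded as untested. It follows from its rules: intention to treat keeps every randomised man in the denominator, and an unlinked record has no event (in the Cox model it is censored). Few events are expected, so a handful of unlinked testers matters. As the plan stands, nobody would know how many there were.

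**Working it through.** **Inputs (Protocol, sample size determination and Randomization).** Control 3.0%, video 15.0%, 87 per arm, power 0.80, alpha 0.05 (sidedness not stated, taken as two-sided), allocation about 1:1.

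**Reproducing the plan's figure.** The two-sided pooled formula without continuity correction is

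n = [1.960·√(2p̄(1−p̄)) + 0.842·√(p1(1−p1)+p2(1−p2))]² / (p2−p1)².

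With p̄ = 0.09, the first root is √0.1638 = 0.4047 and the second is √(0.0291+0.1275) = √0.1566 = 0.3957. So n = (0.7932+0.3331)²/0.0144 = 88.1, or 89 per arm. The unpooled version gives 85.4, or 86. The stated 87 is reproduced to within 2.

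Power at 87 per arm is Φ[(√87·0.12 − 0.7932)/0.3957] = Φ[(1.1193−0.7932)/0.3957] = Φ(0.824) = 0.795. The design has no reserve.

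**Expected events.** Control: 87 × 0.03 = 2.6. Video: 87 × 0.15 = 13.05.

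**Effect of linkage loss.** Let m be the share of testers who cannot be linked, so that observed rate = true rate × (1−m). The documents give no value for m, so the values below are assumptions, equal in both arms.

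| m | Control | Video | Difference | Ratio | Power at 87 per arm | n per arm for 0.80 |
|---|---|---|---|---|---|---|
| 0 | 3.0% | 15.0% | 12.0 points | 5.0 | 0.795 | 89 |
| 5% | 2.85% | 14.25% | 11.4 points | 5.0 | 0.77 | 94 |
| 10% | 2.7% | 13.5% | 10.8 points | 5.0 | 0.75 | 99 |
| 20% | 2.4% | 12.0% | 9.6 points | 5.0 | 0.69 | 113 |
| 30% | 2.1% | 10.5% | 8.4 points | 5.0 | 0.63 | 131 |

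The 20% row in full: p̄ = 0.072; 1.960·√0.1336 = 0.7165; √(0.0234+0.1056) = 0.3592; √87·0.096 = 0.8954; power = Φ[(0.8954−0.7165)/0.3592] = Φ(0.498) = 0.691.

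**The ratio.** Equal loss cancels: 0.15(1−m)/0.03(1−m) = 5.0. The planned hazard ratio hardly moves either. With equal follow-up and proportional hazards it is ln(0.85)/ln(0.97) = 0.1625/0.0305 = 5.3 with no loss, and ln(0.88)/ln(0.976) = 0.1278/0.0243 = 5.3 with 20% loss.

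**Unequal loss, as illustration only.** Losing 10% of control and 20% of video testers gives 2.7% against 12.0%, a ratio of 4.44. The reverse gives 2.4% against 13.5%, a ratio of 5.62. The documents contain nothing that points to either.

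**The case against.** The strongest reply is that linkage is better protected than it looks. The email is typed twice, the system checks its validity before assignment, and at the clinic the coordinator explains face to face why the address is needed before the man consents to give it. The minimal key also looks like a deliberate choice in favour of anonymity. All of this stands. It makes loss less frequent, but it does not make the two addresses agree, and it offers no recovery when they differ.

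The size is also assumed. No mismatch rate is given, and the sample size text does not say whether 3% and 15% are true or measured rates. If they are the rates expected after linkage, the loss is already counted and the power figures above do not apply. At 10% loss the fall is under 5 points.

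How unmatched records are analysed may properly be left to an SAP. The linkage key may not: if no second key is issued at randomisation, no later analysis can create one.

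Three stronger readings are tempting and are not supported:

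- A reader might infer that the comparison is biased. The email is entered before assignment, so the arm cannot cause a false address at baseline. Unequal loss would have to arise afterwards, and the documents give no evidence of it.
- A reader might infer that no email is ever confirmed. The validity check is undescribed, so the Protocol supports neither that statement nor its opposite.
- A reader might infer that throwaway addresses are likely in a hidden population, or that only a character-for-character match will count. The Protocol says neither.

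**Conclusion.** The point holds as a weakness in outcome capture that is cheap to remove. Email is the only link, there is no fallback, and under intention to treat an unlinked tester contributes no event.

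The cost is lost power and a smaller absolute difference. Power falls from about 0.80 to between 0.75 and 0.63 for losses of 10% to 30%. This assumes equal loss in both arms, 3% and 15% as rates before loss, and a two-sided pooled test. The true loss is unknown and could be small. Bias in the ratio is not shown.

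This is a cheap improvement, not an error that invalidates the design. It has to be in place before recruitment starts.

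**What to change.** Show a short random, non-identifying code on the closing screen of both arms, ask the man to bring it, and record it at the clinic alongside the email. Add one sentence to the clinic consent, because Section F now makes linkage conditional on disclosing the email.

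Report the number of clinic attendees who say that they took part online but match no randomised record. Give the result with all of them placed in one arm and then all in the other, noting that some may never have been randomised, so the bounds are wide by design.

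Do not add a second match on age, self-identification or other demographics. It would sit badly with the stated anonymity and consent terms, would need data that the clinic step does not collect, and could create false links.

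The cost is a small change to the website, the clinic form and the consent, and one sensitivity analysis. The code is a mild extra prompt to attend, but it is identical in both arms.

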**Figure 1: Randomization Process**

**Sample size determination**

Our hypothesis is that a video-based intervention compared to a text-based intervention will increase the proportion of HIV testing by 12%. Assuming a proportion of HIV testing of 3.0% in our control intervention and 15.0% in our active intervention, our estimated sample size is 87 participants for each arm of the intervention. This will provide a good power (0.80, at alpha 0.05) to see an absolute difference of 12% in testing proportions between the two arms.

## Limitations:

## Some limitations of our study are: (1) limited generalizability of our results due to the fact that we will recruit a convenience sample (2) selection bias in terms of educational background and age (3) inability to collect data about participants who attended other clinics to receive testing (4) possible self-misrepresentation of some participants leading to misclassification (e.g., a female answering as a male) and (5) inability to measure compliance with the intervention.

## E. Project timeline

| **Project Activities** | **2007** | | | **2008** | | |
| --- | --- | --- | --- | --- | --- | --- |
|  | **April-June** | **July-Sep** | **Oct-Dec** | **Jan-Mar** | **April-Jun** | **Jul-Sep** |
| Administrative preparation (finalize IRB approvals) | *** |  |  |  |  |  |
| Selection Gay websites, focus groups and pilot tests |  | *** |  |  |  |  |
| Recruitment of participants |  |  | *** | *** |  |  |
| Follow-up of participants |  |  | *** | *** | *** |  |
| Data analysis & manuscript preparation |  |  |  |  |  | *** |

## F. Protection of Human Subjects

Our grant proposal will be sent for review to the Institutional Review Board of the University of Washington in Seattle and the NGO Vía Libre in Lima, Peru.

Human Subjects Involvement and Characteristics: We will recruit through Internet MSM 18 years and older who voluntarily are willing to participate in our study and meet the following eligibility criteria: (1) be 18 years of age or older, (2) be a man and report having had sex with men, (3) be a resident of Lima, Peru, (4) answer the survey from Lima, Peru (5) not have been tested for HIV during the last year, (5) have an email address that when typed twice matched and, (6) do not report being HIV positive.

Collection of information:On the Internet, data will be collected via a secure website. The data from the survey will be kept confidential. Only authorized personnel will access the data by logging in using an account name and password. Data that have been exported into statistical software will be stored on an access-controlled computer in a locked room at Via Libre.

Respondents will not be able to access their own or anyone else’s survey. At the homepage of our study, we will tell the participants that they may skip any question they choose not to answer and that the testing for HIV is voluntary and they may decide not to come.

During the survey, respondents will be asked to enter their email address for storage in the database. This email will be later used in the clinic to identify to which arm of the intervention a participant belongs. This will be possible only if the participant discloses his email address through a written informed consent in our site.

Potential Risks: Potential risks of answering the questionnaire include feelings of discomfort or other psychological distress arising from the personal nature of some questions, and the internal conflicts that some men may experience between their values, attitudes, beliefs and behaviors. Potential risks of being tested for HIV include stress, anxiety and depression. If the HIV results are negative it can increase the percentage of unsafe sex which would increase the risk of becoming infected with HIV or other STI. If the tests are positive and get into the wrong hands, the participants may lose their job.

The needle used to draw blood for the tests may cause pain and participants may get a bruise after the procedure.

Recruitment and Informed Consent: Banner ads will run on prominent Peruvian gay websites. The message from the banner ads will be refined during the focus groups. The participants who complete the self-assessment and are randomized on either of the 2 arms of the intervention will have the option of voluntarily go to Vía Libre to get the free tests. Upon arriving at Vía Libre, the participant will be referred to the study coordinator who will explain the risk and benefits of the HIV tests and how the information he provided on the baseline risk assessment will be linked to the arm of the intervention he belongs. After the participant signs the Informed Consent accepting to be tested for HIV and syphilis and accepting to disclose his email, the counselor will perform the pre-test for HIV and collect the email of the participant. Then the participant will be provided with 20 condoms and directed to the laboratory. There, the lab technician will perform a rapid HIV test. If a participant has a positive rapid test for HIV, we will do an ELISA test and then a confirmatory test using Western Blot. We will not ask complete names, addresses, phone numbers, ID numbers or any other form of identification. The results of the HIV and syphilis tests will be stored in a locked cabinet.

Protection against risk: In order to minimize risks of harm and to protect subjects’ rights and welfare, subjects will be provided with our business hours, the email address and telephone number of Vía Libre where they can call if they become distressed and want to talk.

In our study the possibility of discovering suicidal intentions does exist. Should this occur, staff are prepared to address the situation. At Vía Libre there are physicians that can respond in an emergency situation and psychologists that can assess for suicide risk and, if warranted, engage the caller in a no-harm contract and locate appropriate local referral resources. We will follow-up as indicated until the situation is stabilized.

Potential benefits of the proposed research to the subjects and others: An important benefit of the study participants is that they will have the option of getting tested for HIV, syphilis, and receive counseling as well as condoms at no cost, if they are worried about AIDS or any other STI, they might feel better if they receive a negative result. Additionally, knowing a result can also help to diagnose a medical problem or guide health care.

Importance of the Knowledge to Be Gained:The benefits of this research for society could be substantial; the Internet holds great potential not only as a survey research tool, but as a venue for delivering easily accessible, high quality, intervention services. Internet use in Peru is widely available even to people with limited resources. If our work is successful, the approach can be adapted to other populations affected by HIV especially those from developing countries.

